Exclusion criteria at the baseline are: diagnosis of (a) a serious mental disorder (e.g., schizophrenia, schizoaffective disorder, other psychotic disorders, bipolar and related disorders, and personality disorders), (b) a chronic disease resulting in functional impairment, or (c) a neurodevelopmental disorder (e.g., autism spectrum disorders and intellectual disability); history of major depression; being under antidepressant medication; alcohol and/or drug addiction; high-risk pregnancy; and fetal malformations. These criteria were defined to ensure that relevant stress-related heterogeneity at the baseline will be reduced in the study. In addition to these exclusion criteria, mother–child dyads will be excluded from the study (after enrolment) in case of preterm birth (less than 37 weeks of gestational age), very-low weight at birth (less than 1500 g), or unexpected newborn malformations.

Randomization will follow the minimization procedure [67] aiming for a balanced sample size for educational level and age groups at the baseline (18–24 years old, 25–34 years old, and 35–40 years old). Random numbers and their assignment will be sealed in envelopes, kept in sequence and opened consecutively by trained researchers as pregnant women are screened for eligibility and enrolled in the study.

The minimum sample size for MAMH@WORK project will be 159, that is 53 women in each group. Attrition rate is considered to be approximately 40% and thus, a total of 225 pregnant women, 75 in each arm, will be enrolled in the study. These calculations are based on a literature review on psychological interventions for PPD prevention, which found mean depression scores (± standard deviation) of intervention and control groups of 11.00 ± 14.63 and 11.52 ± 14.93, respectively, at the final assessment of the study [39]. These sample size calculations assume the average difference between intervention and control arms reported by Dennis and Dowswell [39], considering a 95% confidence interval and a 80% power of the test to detect a difference between depression scores of both arms. This sample size allows for a medium effect size of the intervention to be detected for depression and anxiety scores.

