### 2.5. Statistical Analyses

Statistical analyses will be performed using IBM/SPSS 26.0 (or a more recent version at the time of data analysis) (IBM Corporation, NY, USA) [70] and R Software (R Foundation for Statistical Computing, Vienna, Austria) [71]. For all statistical analyses, the significance level will be set to α = 0.05.

Two strategies for data analysis will be performed: intention-to-treat (ITT) and per-protocol (PP) analyses. ITT considers all participants allocated to arms at the baseline, thus providing a more conservative estimate of the treatment effect, allowing for noncompliance and protocol deviations. In this case, the last observation carried forward method will be used to deal with missing data. PP analysis includes the subset of participants who completed all evaluations. Results from both types of analyses will be reported when comparing control and intervention groups. For effect size estimation, only PP results will be used, since these allow the identification of the treatment effect under optimal conditions, i.e., without major deviations from the protocol. Sensitivity analyses will be carried out to identify potential effects of data strata and missing data on the outcome.

Univariate description of sociodemographic and outcome variables will be performed by providing central tendency (mean and median) and dispersion (standard deviation and range) measures for each moment of data collection. Normality tests (Kolmogorov–Smirnov test or Shapiro–Wilk test) in combination with kurtosis and symmetry analyses will be used to assess the distribution of the variables under study. Levene´s test will be used to assess homoscedasticity. Baseline between-groups comparisons, i.e., control versus intervention groups, will be tested through ANOVA or its non-parametric equivalent (Kruskal–Wallis) for continuous variables, and chi-square test for categorical variables. Mixed model repeated measure (MMRM) analyses will be used for the analyses of main and secondary outcomes, comparing between control and intervention groups and adjusting for relevant covariates (including potential confounding factors). Mediation and moderation analyses will be explored using structural equation modelling. Conceptually and statistically relevant variables will be selected to adjust the models. The size of the intervention effect will be assessed by calculating Cohen’s *d* coefficient [98] Cramer’s V, and odds ratio.

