## 3. Discussion

The transition to motherhood encompasses numerous changes that require continuous psychosocial adjustment. This places mothers-to-be and recent mothers at an increased risk of developing mental disorders [2,3,4]. At the same time, the perinatal period is a window of opportunity for promoting women’s health/wellbeing and enhancing mother-infant relationships, since these aspects are routinely monitored by healthcare professionals. Here we describe a community-based randomized study protocol to assess the effectiveness of a CBT-based psychoeducation intervention, with or without a biofeedback system, targeting pregnant women at the time of recruitment. MAMH@WORK goes beyond similarly-themed projects (e.g., [100,101]) by adopting an integrated approach in which mother–child relationship, child behavioral, and emotional and cognitive regulation development are addressed, and so is the return to work. Moreover, traditional methods for effectiveness assessment of the intervention are combined with technology-driven approaches providing women with biofeedback on selected physiological indicators. Taking this into consideration, MAMH@WORK emerges as a strategic project for the prevention of mental disorders and for the promotion of mental health and wellbeing during a very challenging period for women and their spouses. Importantly, the intervention will be delivered by trained psychiatrists and psychologists who will follow the referral plan whenever needed, thus contributing for no relevant risks of this intervention to the mother and her child.

Several challenges are anticipated. Recruitment of pregnant women will take place at two different settings (primary health care units and private clinics) and thus, two distinct sociodemographic groups are expected to be enrolled, namely, in terms of their income: pregnant women from high income families have the financial capacity to pay for obstetric appointments at a private clinic, whereas women from low income families will mainly be followed during pregnancy at primary health care centers and public hospitals. Thus, the added-value of this intervention must be stratified according to socioeconomic characteristics. In addition, since the assessment of effectiveness requires repeated measures through time, several strategies to reduce attrition are planned (e.g., periodic telephone contacts, a webpage for project-related communication purposes, and a smartphone app). 

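### The plan names minimisation on education and age group, but describes pre-sealed sequential envelopes that cannot carry it out

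*Protocol article*

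**What the plan says.** Section 2.2 of the protocol article describes allocation in two adjacent sentences.

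- The method: "Randomization will follow the minimization procedure [67] aiming for a balanced sample size for educational level and age groups at the baseline". The age groups are "18–24 years old, 25–34 years old, and 35–40 years old". The number of educational levels is not given.
- The mechanism: "Random numbers and their assignment will be sealed in envelopes, kept in sequence and opened consecutively by trained researchers as pregnant women are screened". The sentence does not end there; its closing clause in full is "as pregnant women are screened for eligibility and enrolled in the study".

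Other statements that bear on this:

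- Section 2.1 describes an open-label trial with three arms.
- Section 2.2 sets 225 women, 75 per arm. It has psychiatrists and psychologists conduct the screening questionnaire and makes a signed consent form a condition of enrolment.
- Section 2.4 lists age and educational level among the data collected to describe the sample and adjust the outcomes.

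**The concern.** Minimisation and a pre-sealed sequence are different procedures. In the first, the arm is worked out when a woman is enrolled, from her age group, her education and the counts of women already allocated. In the second, the arm at each position is fixed before anyone knows who will fill that position. Staff cannot follow both sentences. If they follow the one about envelopes, which is the operational one, the balance promised in the sentence before it has nothing to produce it. An allocation made the wrong way cannot be repaired after enrolment.

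The second issue is timing. The sentence ties the opening of envelopes to screening and to enrolment together, without saying which comes first. It also does not say whether the researchers who open envelopes are separate from those who screen. Eligibility here involves clinical judgement, treatment is open, and several main outcomes are self-reported (HADS, EPDS, happiness, bonding questionnaire). Knowing the arm early could therefore influence who is enrolled.

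**Working it through.** The plan gives no figure on this point to reproduce. The check is first one of logic, then of size.

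**Logic.** With the usual range form of minimisation, a score is computed for each arm k when a new woman arrives:

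S(k) = range across arms of the counts in her age level, if she joined k, plus the same range for her education level.

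The arm with the smallest score is chosen, either always or with a set probability such as 0.8. Both terms need her factor levels and the current counts. An envelope sealed in advance holds neither, so consecutive opening gives the same arm whoever comes next. The two sentences are compatible only if each envelope holds just a random number, used for the random element of minimisation, with the arm computed on the day. But the text puts the assignment in the envelope along with the random number.

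**Size.** Inputs from section 2.2: 225 women, three arms, equal allocation, three age groups. Assumptions not in the documents: age shares of 10%, 60% and 30%; three education levels with shares of 20%, 35% and 45%; age and education independent. There were 2,000 simulated trials for each list and 500 for each form of minimisation. The table shows the mean, with the 95th percentile in brackets.

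| Method | Worst gap between arms within any age or education level | Gap in total arm size |
|---|---|---|
| Pre-sealed simple random list | 14.7 (23) | 14.8 (29) |
| Pre-sealed list in blocks of 6 | 10.9 (17) | 1.2 (2) |
| Minimisation, random element 0.8 | 2.6 (5) | 2.0 (4) |
| Minimisation, deterministic | 1.4 (2) | 1.0 (2) |

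**Hand check of the simple list.** For n women assigned at random to three arms, the expected range of the arm counts is approximately (3/√π) × √(n/3) = 1.693 × √(n/3).

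- All 225 women: 1.693 × √75 = 14.7, against 14.8 simulated.
- The 25–34 group under the assumed 60% share (135 women, 45 expected per arm): 1.693 × √45 = 11.4 for that level alone. Taking the worst of six levels raises the mean to the simulated 14.7.

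Blocking repairs the arm totals but not the balance within levels, because the blocks also ignore age and education.

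**The case against.** The strongest reply is that a journal article condenses the full protocol, and that sealed envelopes opened in order are a recognised way to conceal allocation. That is true, but it does not remove the contradiction. The article does not merely omit detail. It states a method and then a mechanism that cannot deliver it.

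The objection does succeed against several stronger readings that a reader might infer.

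- **That concealment is broken.** The sentence does not stop at screening; it goes on to enrolment, and enrolment requires signed consent. Read whole, it may well mean that envelopes are opened at enrolment. Nothing says that one is opened before eligibility is settled, or that the screeners open them. What stands is that the order and the separation of roles are not fixed.
- **That the arms will end up unequal in size.** This assumes unrestricted simple randomisation, which the article does not state and which the target of 75 per arm does not suggest. With blocks of 6 the mean gap in totals is 1.2.
- **That the balancing factors are left out of the analysis, so that standard errors are too wide.** Section 2.5 says "Conceptually and statistically relevant variables will be selected to adjust the models", so selection is conceptual as well as statistical, and section 2.4 names both factors among the adjustment data. Standard errors become too wide when allocation really balanced on a factor that the model then omits. If the envelopes ignored the factors, unadjusted standard errors would be valid and only precision would be lost. Both harms cannot be claimed together.
- **That recruitment setting had to be a third factor.** The Discussion does say "two distinct sociodemographic groups are expected to be enrolled" because of the two settings. It answers this by calling for results stratified by socioeconomic characteristics, and education is already a balancing factor. Adding setting is a preference, not the correction of an error.

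**Conclusion.** The allocation text is wrong as written: the stated method and the stated mechanism cannot both be used. If the envelopes are used as described, the intended balance on education and age group is not delivered. The mean worst within-level gap between arms would be about 11 to 15 women instead of about 1 to 3. These sizes rest on the assumed factor shares, on three education levels and, for the lower figure, on blocks of 6. The direction does not depend on them, since no fixed list that ignores the factors can target them.

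On concealment, the wording leaves a risk that matters in an open-label trial. The document does not show that concealment fails.

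**What to change.** Before the first woman is allocated, replace the two sentences in section 2.2 with one method that staff can carry out.

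- **Preferred:** minimisation on educational level and age group with a random element, run by a program on the project server. State the number of education levels and the allocation probability. The random element costs little balance (mean worst gap 2.6 against 1.4 for the deterministic form) and makes the next assignment harder to predict. Remove the envelopes.
- **Alternative:** a pre-generated list stratified by education and age group, with a separate set of opaque, numbered envelopes for each stratum, and the minimisation statement deleted. With three levels of each factor this means 3 × 3 = 9 sets. Some would be small: under the assumed shares the smallest stratum would hold about 0.10 × 0.20 × 225 = 4.5 women, so part-filled blocks would leave some imbalance.

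In either case, state that the arm is released only after eligibility is confirmed and consent is signed, and by someone not involved in screening. In section 2.5, name educational level and age group as fixed covariates in the outcome models. Section 2.4 already has both collected for adjustment.

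The cost is a small module in a system that the project is already building, and a change of wording. It needs no extra women, visits or data.

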## 2. Materials and Methods

### 2.1. Study Design and Setting

This is an open-label, three-arm randomized controlled trial of pregnant women who will be followed throughout pregnancy (starting at 28–30 weeks of pregnancy) until 12 months postpartum. The MAMH@WORK project will be conducted at the Environmental Health Institute of Lisbon School of Medicine (ISAMB-FMUL), Portugal, with clinical data being collected at three primary health care units, three hospitals and in a network of private clinics (all part of the MAMH@WORK consortium).

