### 2.2. Sampling Details and Characteristics of the Sample

The target population of this mental health promotion project are pregnant women living in Portugal, with no diagnosis of depression, and employed at the time of recruitment. Women will be recruited at 28–30 weeks of gestational age, since antenatal depression is a relevant predictor for PPD [65,66]; thus, the potential effectiveness of the intervention should increase if it starts during pregnancy. All women booked for delivery at Portuguese hospitals attend various antenatal routine appointments in primary and secondary health care units, which are intended to reduce complications during pregnancy and to improve the chances of positive pregnancy outcomes. These appointments also serve for counselling about health behaviors during the antenatal and postpartum periods. Recruitment will take place in the Lisbon Metropolitan Area from three primary health care units and a network of private clinics. Women at 28–30 weeks of gestation attending an antenatal routine appointment will be invited, by their doctors or nurses, to participate with their babies in the study according to inclusion and exclusion criteria detailed below. In case of agreement, women will be asked to sign a data agreement form and will later receive a formal invitation addressed by the research team. To assess their eligibility to be enrolled in the study, women will be presented with a screening questionnaire conducted by trained psychiatrists and psychologists. In addition, clinical inclusion and exclusion criteria, namely serious mental disorders diagnosed, will be evaluated by antenatal healthcare professionals (i.e., general practitioners, obstetricians, psychiatrists, and psychologists).

To be enrolled in the study, women must meet the following inclusion criteria: native Portuguese speakers or women living in Portugal for at least 5 years; intended pregnancy; primiparous, singleton pregnant women at gestational age of 28–30 weeks; aged 18–40 years; employed; eligible for maternal leave; with access to a smartphone; and have had understood and signed the project’s informed consent form.

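### The protocol names minimisation on age group and education but seals each assignment in sequenced envelopes beforehand; the two rules cannot both be followed

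*Protocol article*

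**What the plan says.** Two adjacent sentences in section 2.2 of the protocol article set the allocation.

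- The first names the method: "Randomization will follow the minimization procedure [67] aiming for a balanced sample size for educational level and age groups at the baseline". The age groups are "18–24 years old, 25–34 years old, and 35–40 years old". The education levels are not listed.
- The second gives the mechanism: "Random numbers and their assignment will be sealed in envelopes, kept in sequence and opened consecutively by trained researchers as pregnant women are screened". It goes on to tie the opening to eligibility screening and enrolment.

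Section 2.1 sets the context: "This is an open-label, three-arm randomized controlled trial of pregnant women". The target in section 2.2 is "a total of 225 pregnant women, 75 in each arm, will be enrolled in the study". The article mentions no allocation computer, running tally, random element or separate envelope series for different kinds of women.

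**The concern.** Minimisation is a rule applied at the moment a woman enters. It looks at her age group and education, counts how many similar women each arm already holds, and favours the arm that most reduces the imbalance. A sequence of sealed assignments is fixed in advance and takes no account of who opens the next envelope. A team following the text must break one sentence or the other.

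Each choice has a cost. If the envelopes are followed, the trial does not have the balance it announces. If minimisation is followed, the envelopes no longer hide the next arm, and concealment depends on arrangements the article does not describe. Concealment matters here because the trial is open-label and many main maternal outcomes are self-reported (HADS, EPDS, the happiness item and the PBQ). Foreknowledge of the next arm would allow selective enrolment, and adjusting for measured covariates does not remove that bias.

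**Working it through.** The article gives no figure for allocation, so there is none to reproduce. The check sets the two sentences against each other and then sizes each way of resolving them.

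**1. Can both be followed?**

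- Minimisation: arm = function of (her age group, her education, totals so far, possibly a random draw). None of the first three is known before she enters.
- Envelopes: arm = the content of envelope number *i*, fixed before she enters.

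The second has none of the first's inputs. Two readings might reconcile them:

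- The envelopes could hold only random numbers for ties or a biased coin. But the text seals the assignment as well as the number.
- There could be one envelope series per age-by-education cell. That is stratified randomisation rather than minimisation, and the text describes a single sequence.

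**2. If the envelopes govern: loss of balance**

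Inputs from the article: N = 225, three arms, three age groups. Assumed, because the article does not give them: age shares 10/65/25%, and three education levels with shares 20/35/45% (set A, 600 simulated trials per method) or 20/40/40% (set B, 400 per method). The gap at a factor level is the largest minus the smallest arm count. The worst-level gap is the largest of the six gaps.

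| Allocation | Mean worst-level gap, A (B) | 95th percentile, A | Mean arm-size gap, A (B) |
|---|---|---|---|
| Simple random list | 14.8 (15.2) | 24 | 14.4 (14.4) |
| List in blocks of 6 | 10.5 (not run) | 16 | 1.2 (not run) |
| Deterministic minimisation | 1.3 (1.3) | 2 | 1.1 (1.0) |
| Minimisation, 0.8 random element | 2.1 (2.4) | 3 | 1.7 (1.9) |

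Relative to deterministic minimisation, a fixed list gives 10.5/1.3 ≈ 8 to 14.8/1.3 ≈ 11 times the worst-level gap.

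Hand check: the expected range of three independent normal values is (3/√π) × SD = 1.693 × SD.

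- Arm-size gap, simple list: 1.693 × √(225/3) = 1.693 × 8.66 = 14.7, close to the simulated 14.4.
- One factor level with share *p*, arms fixed at 75: roughly 1.693 × √(75*p*(1 − *p*)). This is 4.4 women at *p* = 0.10, 5.9 at 0.20 and 7.3 at 0.50.

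So a list that gives exactly 75 per arm still leaves an expected gap of about 4 to 7 women at any single level with a share between 10% and 50%. The worst of six levels is larger, in line with the simulated 10.5. The size depends on the assumed shares; the direction does not.

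**3. If minimisation governs: predictability to someone who sees the totals**

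| Method | Correct guesses of the next arm, A (B) |
|---|---|
| Chance | 33% |
| Deterministic minimisation | 76% (78%) |
| 0.8 random element | 67% (68%) |

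In set A under the deterministic rule, one arm is the sole minimum for 56% of women, so their arm is fully determined. The other 44% are ties, guessed correctly in (0.760 − 0.559)/(1 − 0.559) = 46% of cases. That lies between 1/3 (three-way tie) and 1/2 (two-way tie), as it should. The random element lowers the guess rate by only about 10 percentage points, so hiding the totals does most of the work.

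**The case against.** Much can be said against reading this as a serious failure.

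- **Who computes the arm.** A reader might infer that researchers at the clinics would work out the next arm from visible totals. The article does not say so. In section 2.2 clinic doctors and nurses invite, the research team sends the formal invitation, and psychiatrists and psychologists screen. Who holds the tallies, and whether there is a random element, are details an article commonly leaves to the full protocol. The guess rates are therefore conditional.
- **Arm sizes.** A reader might infer that 75 per arm would be lost. That holds only for an unrestricted list. A prepared or blocked list keeps arm sizes at or near target. Even a 14-woman gap, say 82/75/68, raises the standard error of the widest pairwise contrast by a factor of only √[(1/82 + 1/68)/(2/75)] = 1.004.
- **Several sites.** Because "Recruitment will take place in the Lisbon Metropolitan Area from three primary health care units and a network of private clinics", a reader might infer that one envelope series must serve several places. Nothing shows where the envelopes are opened, and section 2.1 places the project at one institute.
- **Consequence of imbalance.** Chance imbalance does not bias a randomised comparison. Section 2.4 collects age and education for adjustment, and section 2.5 plans mixed models with relevant covariates.
- **Outcomes.** Not all main outcomes are self-reported. The CARE-Index and the Strange Situation Procedure are videotaped.

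These points stand, and they limit the consequences. They do not remove the contradiction: the article states both rules outright, so this is not a detail left to a fuller document.

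**Conclusion.** The allocation procedure is wrong as written, because its two sentences describe different methods and no team can carry out both.

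If the envelopes govern, the promised balance on age group and education is not delivered: a mean worst-level gap of about 10 women (blocked list) to 15 (simple list), against about 1 to 2 under minimisation. The planned covariate adjustment softens this. If minimisation governs, sealed envelopes cannot provide the concealment. Allocation would then be partly predictable, but only to someone who can see the running totals, a matter the article leaves open.

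The gaps rest on assumed factor shares and an assumed three education levels. The guess rates also assume full sight of the totals. The documents do not support going further and saying that 75 per arm is necessarily lost, that clinic researchers would compute the arm, or that one envelope series has to cover several sites. The contradiction should be settled before the first woman is allocated, since allocation cannot be repaired afterwards.

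**What to change.** Choose one method and delete the other.

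**Preferred.** Replace the envelope sentence with: *Allocation is by central computerised minimisation on age group and educational level, with a random element (preferred arm with probability 0.8). Running totals are hidden from recruiting and screening staff, and the arm is released only after eligibility and consent are recorded.* The cost is a wording change and a short script or web form; section 2.4 already plans a server and section 2.5 names R. Balance is slightly looser than under deterministic minimisation (mean worst-level gap about 2 rather than 1.3).

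**Alternative.** Keep sealed envelopes, drop the word *minimization*, and use pre-generated randomisation in blocks of varying size, stratified by age group and education, with one envelope series per stratum. The cost is incomplete blocks in thin strata. With the assumed shares, the smallest of nine cells would expect 225 × 0.10 × 0.20 = 4.5 women, so balance there would be loose.

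Either repair is adequate, and the 0.8 weight is one reasonable choice among several.

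### Enrolling 225 women does not keep the stated minimum of 159 after 40% attrition: about 135 (45 per arm) would remain

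*Protocol article*

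**What the plan says.** The sample size paragraph in section 2.2 of the protocol article makes two linked statements. The first fixes the number needed: "The minimum sample size for MAMH@WORK project will be 159, that is 53 women in each group". The second allows for losses: "Attrition rate is considered to be approximately 40% and thus, a total of 225 pregnant women, 75 in each arm, will be enrolled". The abstract repeats the total of 225. No other attrition rate, and no other reason for 225, appears in the article.

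The same paragraph gives the statistical basis as "considering a 95% confidence interval and a 80% power of the test to detect a difference between depression scores of both arms" and concludes: "This sample size allows for a medium effect size of the intervention to be detected for depression and anxiety scores". It puts no number on a medium effect. Section 2.5 says "the significance level will be set to α = 0.05", without saying whether tests are one- or two-sided.

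Section 2.5 also bears on who counts after attrition. The main and secondary outcomes are to be analysed by MMRM. The intention-to-treat analysis keeps everyone allocated and fills gaps by last observation carried forward. The per-protocol set is limited to women with every assessment done, and effect sizes are to be estimated from that set alone.

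**The concern.** The second statement presents 225 as the consequence of the minimum and the attrition rate. Anyone who applies the stated rate to the stated enrolment gets fewer women than the stated minimum, so 159, 40% and 225 cannot all stand.

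The minimum is the number on which the sensitivity claim rests. If the attrition allowance is too small, the article overstates how many women will complete and how small an effect the completer analysis can detect. This matters here because effect sizes will come from completers only. It also leaves the trial without a correct figure for how much loss it can bear, although sections 2.4 and 3 describe several measures to limit attrition.

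**Working it through.** **Inputs, all from section 2.2:** minimum 159 (53 per arm); attrition 0.40; enrolment 225 (75 per arm); three equal arms.

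**1. Reproducing 225.**
- Multiplying by (1 + attrition): 53 × 1.4 = 74.2, rounded up to 75 per arm; 75 × 3 = 225. This matches exactly. On the total, 159 × 1.4 = 222.6, so the per-arm route is the likelier one.
- Dividing by (1 − attrition): 53/0.6 = 88.3, rounded up to 89 per arm, or 267; on the total, 159/0.6 = 265. Neither is near 225.

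That the multiplicative form was used is an inference, because the article shows no formula. The remaining steps do not depend on it.

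**2. Completers expected from 225 at 40% attrition.**
- 225 × 0.6 = 135; 75 × 0.6 = 45 per arm.
- Shortfall: 159 − 135 = 24 women, and 24/159 = 15%; per arm, 53 − 45 = 8.

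**3. Attrition that 225 can bear.**
- 1 − 53/75 = 0.293, so retention must be at least 53/75 = 0.707.

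| Attrition | Women left per arm (of 75) | Enrolment per arm needed to keep 53 |
|---|---|---|
| 29% | 53.25 | 75 |
| 30% | 52.5 | 76 |
| 35% | 48.75 | 82 |
| 40% | 45 | 89 |

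**4. What the shortfall means for sensitivity.** The article does not define a medium effect, so the conventional values f = 0.25 and d = 0.5 are assumptions here, as is a two-sided test at 0.05. The counts are completers.
- One-way ANOVA with three arms, noncentrality N × f². For N = 159 this is 159 × 0.0625 = 9.94, power 80.5%. For N = 135 it is 135 × 0.0625 = 8.44, power 73.2%.
- Two-sample t-test, no adjustment for multiple comparisons, d = 0.5: power 72.2% with 53 per arm and 65.0% with 45.
- Same t-test, d detectable with 80% power: 0.549 with 53 per arm and 0.597 with 45. The normal approximation, (1.96 + 0.84) × √(2/n), gives 0.544 and 0.591.

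Under the ANOVA assumption the required total is 157.2, which rounds up to 53 per arm. So f = 0.25 is a plausible origin of the minimum, though the article does not say so.

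**The case against.** **The rate is only approximate.** It is, but 225 needs attrition of about 29%. Even 35% leaves fewer than 49 per arm.

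**The planned analyses do not discard women who leave.** This stands in part. An MMRM uses the visits that a woman completed before leaving, and there are five data collection moments. The 45-per-arm power figures are therefore not the power of the main model. But the article's own step treats 159 as the number needed after attrition, carrying a last observation forward adds no information, and effect sizes come from completers alone.

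**Attrition destroys the stated 80% power.** A reader might infer this stronger claim, and the documents do not support it, for two further reasons:
- The article ties its 80% to a cited difference, with means and standard deviations for "intervention and control groups of 11.00 ± 14.63 and 11.52 ± 14.93, respectively". That is 0.52/14.78 = 0.035 standard deviations. Two-sided power for it is about 5% with either 53 or 45 per arm, so attrition barely matters on that basis. How 159 was obtained is a separate question.
- Read as a pairwise comparison at d = 0.5, power is already 72% with the full 53 per arm. A fall from about 80% appears only under the assumed three-arm ANOVA.

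**Exclusions after enrolment make it worse.** Section 2.2 also removes dyads after preterm birth, very low birth weight or newborn malformation. The article does not say whether the 40% includes them, so no further loss can be put in figures.

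**Conclusion.** The attrition step is wrong as written. With the article's own rate, 225 enrolled gives about 135 completers (45 per arm), 24 short of the stated minimum. The minimum survives only if attrition stays at or below about 29%, or if 265 women (267 with equal arms) are enrolled. This conclusion uses only the three stated figures and needs no assumption about the effect, the test or the formula used.

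The loss of sensitivity is conditional. If medium means f = 0.25 in a three-arm ANOVA at 0.05, power among completers falls from 80.5% to about 73%. For an unadjusted two-sided pairwise t-test, the effect detectable with 80% power rises from d of about 0.55 to about 0.60. Both describe the per-protocol analysis. The documents do not allow the power of the MMRM to be worked out.

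**What to change.** Keep the enrolment of 225 and correct what is said to follow from it in section 2.2:
- State that, at 40% attrition, about 135 women (45 per arm) are expected to complete.
- State that the minimum of 159 is kept only if attrition is at most about 29%, that is, retention of at least about 71%. Monitor the retention measures against that benchmark.
- Say whether the 40% includes the dyads removed after enrolment.
- Define the medium effect and restate what completers can detect, with the assumptions beside the figures: about 73% power for a three-arm f = 0.25 at 0.05, or 80% power for an unadjusted two-sided pairwise d of about 0.60. Label these as per-protocol figures, not as the power of the MMRM.

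The cost is a few reworded sentences and a slightly less favourable statement of sensitivity; nobody extra is recruited. If the sponsor prefers to secure 159 completers at 40% attrition, the target becomes 265, or 267 with equal arms, which is 40 to 42 more women.
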